### Randomization and allocation

Patients who meet the inclusion criteria, successfully converted to sinus rhythm and were confirmed by electrocardiogram immediately after ablation will be enrolled. Randomization will be performed after the ablation. After eligible patients sign the informed consent, baseline information will be collected, including basic information, medical history, preoperative medication history, electrocardiogram and laboratory results. Researchers will randomly allocate eligible patients at a 1:1 ratio to receive sacubitril/valsartan or not. This trial will be randomized using a dynamic stratified block group randomization method. The R package blockrand (R version 4.1.2) was used to generate a randomization table with a specified sample size, and the block sizes were randomized among 4, 6, and 8 to form the randomization pool for this trial. The trial was stratified by research centers, each of which was assigned random numbers for a block unit by “first-come, first-served”, and the random number for the next block was available in the randomization pool only when the random number for that block was used up. The process of generating the randomization table and assigning randomized numbers for this study was carried out by an independent researcher who was not involved in recruitment and subsequent interventions. After a subject had consented to participate in the trial, the recruiting physician queried the randomization number from the investigator in charge of randomization, who provided the patient's treatment allocation plan based on the participant's center and order of inclusion, as well as marked the grouping on the randomization table.

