#### Secondary outcome

The secondary endpoint will be the sinus rhythm maintenance rate at 3 and 6 months and incidence of MACE at 3, 6, and 12 months. Cardiovascular re-hospitalization at 3, 6, and 12 months will be aggregated in HFpEF patients with AF and patients with AF and otherwise normal cardiac function. Changes in cardiac structural function indicators will be observed at 3, 6, and 12 months. Echocardiographic parameters such as LAD, LAVi, LAEF will be recorded or calculated.

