### Sample size

The determination of the sample size in this study will be driven by the need of the above strategy to detect sacubitril/valsartan over conventional drugs.

The recurrence rate of atrial fibrillation after 12 months in patients with persistent AF is approximately 42% (15), and we expect a 20% decrease in the incidence of primary endpoint events taking ARNI after catheter ablation in patients with persistent AF. Under the assumption based on the exponential distribution, the risk ratio is 0.46.

Based on the above assumptions, the expected enrollment time is 24 months, without considering the mid-term analysis, and the minimum follow-up time is 12 months. Assuming a 20% missing visit in each of the control and trial groups, the study requires 450 participants (225 trial group, 225 control group) to obtain 90% difference at a significance level of *a* = 0.05 (unilateral). The sample size is calculated by PASS15.0 software. The interim analyses is set up by the O'Brien-Fleming method to control the overall Type I error below 0.05. The final sample size will be 462 cases (231 trial group, 231 control group).

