### Statistical and analytical plans

The statistical analysis will be along with the intention-to-treat (ITT) principles. The ITT population will include patients who meet the criteria, are randomized, and take at least one dose of drugs after being enrolled. For statistical description, continuous variables are described by using mean and standard deviation if they satisfy a normal distribution, skewed distributions are described by medians and quartiles, while categorical variables will be presented as frequency or percentage in each category. For the baselines, the t-test is used to compare the differences for quantitative variable if the data meets the normality test, otherwise, the data will be transformed or rank sum test. Categorical variables such as disease history and smoking history can be tested using chi-square test or rank sum test. For outcomes such as 239sinus rhythm maintenance rate, all-cause death, re-hospitalization rate for cardiovascular causes and MACE, Kaplan-Meier curves will be used to characterize how the probability of an endpoint event changes with survival time, and comparisons between survival curves will be carried out using log-rank tests. We used cox proportional hazards models to estimate hazard ratios and 95% confidence intervals. Cardiac structural function indicators will be described by mean value (±SD) or median and quartiles, and the sphericity of the covariance array will be tested by the Mauchly method. If the data satisfies the sphericity of the covariance array, the analysis of variance with repeated measures data will be used for group comparisons of each indicator. If it is not satisfied, the Greenhouse-Geisser method will be used for comparison of differences. Missing observations will be accounted for using the predictive mean matching (PMM) method. If the missing data is numerical, it will be filled by predictive mean matching; meanwhile if the missing data is non-numerical, logistic regression and discriminant functions will be used to fill it. The *p*-value threshold is 0.05(*p* < 0.05), and when it is below this threshold, indicating that the difference is statistical significant. SPSS statistical software (SPSS Inc, Chicago, IL, USA, version 23) will be used to analyse data.

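### Baseline adjustment of the secondary echo endpoints, and centre strata in the log-rank and Cox analyses, would be a near-free gain in precision; the issue is minor and the primary conclusion is not threatened

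*Protocol article*

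**What the plan says.** **Echo endpoints.** Under Secondary outcome: "Changes in cardiac structural function indicators will be observed at 3, 6, and 12 months". LAD, LAVi and LAEF are the named parameters, and atrial structure is part of the secondary objective. Under Statistical and analytical plans, sphericity is checked by Mauchly's test, "the analysis of variance with repeated measures data will be used for group comparisons of each indicator" if it holds, and Greenhouse-Geisser is used if it does not. No baseline covariate is named, and the text does not say whether baseline is one of the repeated levels. Missing numerical values are to be filled by predictive mean matching.

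**Time-to-event outcomes.** The same section says that "comparisons between survival curves will be carried out using log-rank tests" and "We used cox proportional hazards models to estimate hazard ratios and 95% confidence intervals". It mentions neither strata nor covariates.

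**Randomisation.** Under Randomization and allocation: "The trial was stratified by research centers". There are three centres.

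**Design effect.** Under Sample size, 12-month recurrence without the drug is put at about 42%; "we expect a 20% decrease in the incidence of primary endpoint events"; and "Under the assumption based on the exponential distribution, the risk ratio is 0.46".

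**The concern.** The echo section goes further than naming a family of methods: it fixes the sphericity test, the fallback correction and the imputation method. The method chosen does not make efficient use of the baseline measurement.

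- If baseline is a repeated level, the group main effect averages in a time point at which randomisation makes the true difference zero.
- If baseline is left out, its predictive value is lost.
- If change from baseline is analysed, baseline is subtracted with a fixed weight of 1 instead of its regression weight.

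Each route gives a noisier treatment comparison than baseline adjustment. The loss falls on the structural endpoints.

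Separately, restricted randomisation by centre balances the arms within centre. A test that leaves centre out does not take credit for that balance, so it is somewhat conservative when recurrence differs between centres. What is at stake there is a little power, not validity.

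**Working it through.** **1. Design ratio.** Reading the 20% decrease as absolute, 42% falls to 22%. Under exponential times, HR = ln(0.78)/ln(0.58) = 0.456, which reproduces the stated 0.46. This is the effect at which the primary limb should be judged first.

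**2. Echo, inputs.** 231 per arm less 20% missing gives 231 × 0.8 = 184.8, about 185 per arm (from Sample size). The documents give no effect size or correlation for the echo measures. I assume a true difference d = 0.2 SD at each follow-up visit, equal correlation r between all visits, and a two-sided 5% test.

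**3. Echo, formulas** (variance per patient in SD² units, for the mean over visits):
- Baseline as a fourth level, group main effect: variance (1+3r)/4, effect 0.75d
- Follow-up visits only: variance (1+2r)/3, effect d
- Change from baseline: variance (1+2r)/3 + 1 − 2r, effect d
- Baseline as covariate: variance (1+2r)/3 − r², effect d

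Power = Φ(effect/√(2 × variance/185) − 1.96).

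**4. Echo, results.**

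| Analysis | Variance, r = 0.5 | Power | Variance, r = 0.7 | Power |
|---|---|---|---|---|
| Baseline as a level | 0.625 | 45% | 0.775 | 37% |
| Follow-up only | 0.667 | 65% | 0.800 | 58% |
| Change from baseline | 0.667 | 65% | 0.400 | 86% |
| Baseline as covariate | 0.417 | 85% | 0.310 | 93% |

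Example, covariate at r = 0.5: √(2 × 0.417/185) = 0.0671; 0.2/0.0671 = 2.98; Φ(1.02) = 85%.

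With baseline as a level, the group-by-time interaction could be tested instead of the main effect. The squared deviations of (0, 0.2, 0.2, 0.2) about their mean of 0.15 sum to 0.03. The noncentrality is therefore (185/2) × 0.03/(1−r), that is 5.55 at r = 0.5 and 9.25 at r = 0.7. On 3 degrees of freedom this gives 48% and 72% power.

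**5. Why the ranking is general.** Follow-up-only variance exceeds the adjusted variance by r². Change-score variance exceeds it by (1−r)². For r = 0.3/0.5/0.7/0.8, adjusted variance is 0.83/0.63/0.39/0.26 of follow-up-only and 0.48/0.63/0.78/0.85 of change from baseline.

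**6. The 12-month difference alone.** The figures in step 4 are for the average over three visits. For the 12-month value on its own, the variances are 1 (follow-up only), 2−2r (change) and 1−r² (covariate). At r = 0.5 these are 1, 1.00 and 0.75, with power 49%, 49% and 60%. At r = 0.7 they are 1, 0.60 and 0.51, with power 49%, 70% and 77%. Power is lower throughout, but adjustment still does best.

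**7. Primary outcome.** This was simulated: 4,000 trials per scenario, N = 462, 12-month follow-up, 20% dropout, a single two-sided 5% log-rank test. The centre split of 50/30/20% and the centre recurrence rates are assumptions. Each cell shows unstratified / centre-stratified rejection.

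| Control recurrence by centre | HR 0.456 | HR 0.60 (assumed) | HR 1 (type I error) |
|---|---|---|---|
| 42/42/42% | 99.2 / 99.2% | 86.6 / 86.3% | 5.2 / 5.2% |
| 33/45/59% | 99.3 / 99.4% | 85.5 / 86.9% | 4.6 / 5.2% |
| 27/47/72% | 99.1 / 99.5% | 83.0 / 86.6% | 3.3 / 4.3% |

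Monte Carlo error is about 0.3 points for type I error and 0.6 points for power near 86%.

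**The case against.** **Silence is not a choice.** The article names test families. It does not say that the log-rank test is unstratified or the Cox model unadjusted, and an analysis plan that is not shown may well carry centre. This stands for the centre limb: a reader might infer that the analysis disregards its randomisation strata, but the documents show only that the section does not carry them over.

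**Baseline is not discarded.** A reader might also infer that baseline echo values are ignored. The endpoint is worded as changes, so baseline enters in some form. This stands too. What can be said is that no form of entry open to the stated ANOVA matches covariate adjustment.

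**The comparator matters.** Setting 37% against 93% compares adjustment with the least favourable reading. Against change from baseline, the reading closest to the endpoint's wording, the gain is about 20 points at r = 0.5 and 7 at r = 0.7. This is the fairer measure.

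**The primary cost is small.** A material loss needs an effect weaker than the design ratio and large centre differences, and the documents give neither. They suggest similar centres: one province, one ablation technique, one mapping system and no additional lines. This stands.

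**Missing visits.** Classical repeated-measures ANOVA needs complete rows, but the plan fills numerical gaps by a stated method. Preferring a model on observed visits is a methodological preference; the filling-in is not a defect.

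**Conclusion.** The point holds as a minor, near-free improvement, mainly for the secondary echo endpoints. In every scenario computed, baseline adjustment is more precise than any form in which baseline could enter the stated ANOVA. The gain over change from baseline is about 20 to 7 points of power, and larger over the other forms. The size rests on an assumed 0.2 SD effect, equal correlations of 0.5 to 0.7 and 185 per arm; the ranking against follow-up-only and change scores does not depend on the effect size.

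For the primary outcome, the stronger reading that leaving centre out weakens or invalidates the main test is not supported. The unstratified test is valid, and conservative if centres differ. The loss is under 0.5 points at the design ratio of 0.46, 0 to about 4 points at an assumed hazard ratio of 0.60, and none if centres are alike. The primary conclusion is not threatened.

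**What to change.** **Echo endpoints.** Replace the repeated-measures ANOVA by a linear mixed model on the 3, 6 and 12-month values, with baseline value, centre, visit, treatment and treatment-by-visit, and an unstructured covariance across visits. Use all observed visits and report the treatment difference at 12 months with its confidence interval.

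**Time-to-event outcomes.** As a companion change, state that the log-rank test and Cox model are stratified by centre, for sinus rhythm maintenance and likewise for MACE and cardiovascular re-hospitalisation.

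**Cost.** Wording and analysis code, with a few more terms in the models. Centre is known for every patient. A baseline echo is implied by the change endpoints and by the ejection-fraction exclusion; the team should confirm that LAD, LAVi and LAEF are recorded from it. The article reports that recruitment is under way, so the change should be fixed before outcome data are compared by arm.

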### Outcome measurements

#### Primary outcome

The primary endpoint of the study will be the sinus rhythm maintenance rate within 12 months determined by at least the 24-hour Holter electrocardiogram. Patients will be given the Holter electrocardiogram at 3, 6 months and 12 months.

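### The imputation rule does not exempt the event outcomes, so read literally it fills a missing rhythm status that the planned survival analyses would censor

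*Protocol article*

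**What the plan says.** All the analysis statements are in the protocol article under Statistical and analytical plans.

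- **Event outcomes.** For sinus rhythm maintenance, all-cause death, cardiovascular re-hospitalisation and MACE, "Kaplan-Meier curves will be used to characterize how the probability of an endpoint event changes with survival time". In addition, "comparisons between survival curves will be carried out using log-rank tests", and the effect estimate is a Cox hazard ratio: "We used cox proportional hazards models to estimate hazard ratios and 95% confidence intervals".
- **Echocardiographic measures.** Subject to a sphericity check, "the analysis of variance with repeated measures data will be used for group comparisons of each indicator".
- **Missing data, general rule.** "Missing observations will be accounted for using the predictive mean matching (PMM) method". No variable is named and none is excluded.
- **Missing data, by type.** Numerical values are filled by predictive mean matching; "meanwhile if the missing data is non-numerical, logistic regression and discriminant functions will be used to fill it".

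Two statements elsewhere bear on this. Under Primary outcome, "Patients will be given the Holter electrocardiogram at 3, 6 months and 12 months". Under Sample size, the allowance for loss reads "Assuming a 20% missing visit in each of the control and trial groups".

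**The concern.** Kaplan-Meier, log-rank and Cox need an event indicator and a time for each patient. A patient lost while still in sinus rhythm contributes follow-up to the last assessment and is then censored. A general rule that fills missing non-numerical observations reaches the same patient by another route. It supplies a yes/no status from a logistic or discriminant model, but no time at which a filled event happened. The section does not say which route applies.

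The two routes can give different p-values and hazard ratios for the primary endpoint. In an open-label trial that choice should be fixed in writing before results are seen. It also touches the interim analyses, which are triggered at 33% and 67% of planned primary events: the text leaves open whether a filled event would count towards those totals.

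**Working it through.** **Does the rule reach event status?** The article never says so, and this step is inference from unrestricted wording.

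1. The echocardiographic measures named (LAD, LAVi, LAEF) are numerical, so predictive mean matching already serves them.
2. The non-numerical clause therefore has two candidates among the stated analyses: baseline categories and follow-up event status.
3. Baseline categories are collected at enrolment and enter only the baseline comparisons. No covariate-adjusted outcome model is stated.
4. The only missingness the article anticipates is missed visits, 20% in each arm. The Holter that determines the primary endpoint is done at those visits.

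Read literally, the clause therefore covers rhythm status.

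**How many patients?** Twenty per cent of 462 is about 92, but patients who recur before they are lost already have a known outcome. Assume exponential dropout reaching 20% at 12 months and the article's event rates of 42% (control) and 22% (42 minus 20 points; ln 0.78 / ln 0.58 = 0.456, which agrees with the stated 0.46). The share lost before any event is d/(l+d) × [1 − exp(−(l+d))], where d = −ln 0.80 = 0.223 and l = −ln(1 − event rate).

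- Control: l = 0.545; 0.223/0.768 × (1 − 0.58×0.80) = 0.156, about 36 of 231.
- Trial: l = 0.248; 0.223/0.472 × (1 − 0.78×0.80) = 0.178, about 41 of 231.

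So about 77 of 462 patients, or 16% to 18% per arm.

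**What would filling do to the error rate?** The article states no figure that could be reproduced here, so this was checked in two ways.

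*Binary approximation.* For a single fill of a fraction m = 0.20 with arm in the model, the true variance relative to the reported one is

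- 1/(1−m) + m = 1.25 + 0.20 = 1.45, or
- 1.45 + m²/(1−m) = 1.45 + 0.05 = 1.50, if the fill probability is itself drawn.

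A nominal two-sided 5% becomes 2Φ(−1.96/√1.45) = 10.4%, or 2Φ(−1.96/√1.50) = 11.0%. A simulation of this binary case (231 per arm, 32% event rate, 4,000 runs) gave 12.0%.

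*Log-rank simulation, closer to the planned test.* 462 patients, 42% events in both arms, visits at 3, 6 and 12 months, exponential dropout unrelated to outcome, 6,000 runs (simulation error about 0.3 to 0.4 points). Assumptions not in the article: the filled time is set to 12 months, and the filling model holds arm only or nothing. The pooled imputation row tests the 12-month risk difference, not the log-rank.

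| Handling | Two-sided error, 20% v 20% dropout | 25% (trial) v 15% (control) |
|---|---|---|
| Censoring | 5.0% | 5.2% |
| Single fill, arm in model | 9.2% | 9.7% |
| Single fill, arm not in model | 4.8% | 5.6% |
| Ten imputations, pooled by Rubin's rules | 5.2% | 5.8% |

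The single fill with arm gave a standard deviation of the z statistic of 1.165, and 2Φ(−1.96/1.165) = 9.2%, which agrees with the table. At the stated final-look threshold of 0.0313 (z = 2.153), taken as two-sided, the same spread gives 2Φ(−2.153/1.165) = 6.5%.

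**What would filling without arm do to the effect?** Missing patients in both arms get the same event probability, so the difference shrinks to about (1 − 0.20) × 20 = 16 points. The binary simulation gave 15.9. At the planned effect, simulated power was at least 98% under all four approaches, so the cost here is a biased estimate more than a lost test.

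**The case against.** The strongest defence is that the rule was not meant for event outcomes. It speaks of missing observations, not missing outcomes, and it comes straight after the repeated-measures analysis of the echocardiographic data, which needs complete visits. The non-numerical clause could serve categorical baseline items such as disease and smoking history. Naming Kaplan-Meier, log-rank and Cox already implies censoring, and a patient lost in sinus rhythm at month 6 has an observed time and status. That no method is given for imputing event times points the same way. This reading is plausible and may be what the authors intend. It still has to be read into a sentence that is written without limits, and the only missingness the article foresees is at the visits that determine the primary endpoint.

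A reader might go further and infer that dropouts will be given an invented outcome from a single filled data set, so that the trial's error rate is not controlled. The article does not support that. It does not state that event status will be imputed, and the verb it uses does not settle whether imputation is single or multiple. The methods it names are ordinary components of multiple imputation. The number of imputations and the pooling may stand in an analysis plan that is not shown, and their absence from an article is no fault. Inflation appears in only one of the four approaches examined.

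Two further points stand. One in five overstates the share of patients affected. And MACE, survival and re-hospitalisation are asked about by telephone, so a missed clinic visit need not leave them missing; the exposure is mainly on the Holter-based endpoint.

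**Conclusion.** The point holds as a conflict between a stated rule and the stated analyses. The imputation rule is unrestricted and is not reconciled with the censoring that the survival methods imply. It deserves correction because it reaches the primary endpoint as written, but it does not show that the trial's error rate is lost.

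The size is conditional. A single fill of event status with arm in the model would give a two-sided type I error of roughly 9% in place of 5% by the log-rank simulation; the 10% to 12% of the binary calculations does not represent the planned test as closely. A fill without arm leaves the error near 5% but dilutes the difference. Censoring and properly pooled multiple imputation both keep it near 5%. These figures assume that the 20% missing visits mean 20% of patients lost per arm, for reasons unrelated to outcome.

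**What to change.** In Statistical and analytical plans, replace the general missing-data rule with two statements:

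1. Event outcomes are not filled. Sinus rhythm maintenance is right-censored at the last rhythm assessment; MACE, death and cardiovascular re-hospitalisation are right-censored at the last contact.
2. Predictive mean matching and the logistic or discriminant methods apply only to echocardiographic and baseline variables, and are carried out as multiple imputation.

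If the investigators do want to impute event outcomes, that is defensible only as multiple imputation of event times with proper pooling, and the text should say so. A sensitivity analysis that counts a missing Holter as recurrence in both arms is optional.

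The cost is a few sentences, an amendment and a little programming, with no extra patients or visits. Intervals will be slightly wider than a filled data set would show.

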Interim analyses of key safety and endpoint metrics will be conducted periodically during the course of the trial. Two interim analyses will be conducted when 33% and 67% of the total number of planned primary endpoint events have been reached. Interim analyses will be performed using the O'Brien-Fleming method to maintain an overall significance level of 0.05. The significance level alpha for the two interim and final analyses is 0.0015, 0.0172, and 0.0313, respectively. The independent Data Monitoring Committee will review the safety and efficacy of the trial based on interim analysis results.

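### The interim and final significance levels (0.0015, 0.0172, 0.0313) are O'Brien-Fleming alpha increments, not p-value cut-offs, and the general p < 0.05 rule makes no exception for the final primary test

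*Protocol article*

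**What the plan says.** The Sample size section sets alpha "at a significance level of *a* = 0.05 (unilateral") and says of the interim looks: "The interim analyses is set up by the O'Brien-Fleming method to control the overall Type I error below 0.05". 

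The Statistical and analytical plans section gives the timing: "Two interim analyses will be conducted when 33% and 67% of the total number of planned primary endpoint events have been reached". It names the target, "Interim analyses will be performed using the O'Brien-Fleming method to maintain an overall significance level of 0.05", and then the level for each look: "The significance level alpha for the two interim and final analyses is 0.0015, 0.0172, and 0.0313, respectively". 

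The preceding paragraph of that section covers baseline comparisons, the survival outcomes (including sinus rhythm maintenance) and the repeated echocardiographic measures. It closes with one general rule: "The *p*-value threshold is 0.05(*p* < 0.05), and when it is below this threshold, indicating that the difference is statistical significant". 

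The article does not say whether the three figures are alpha spent or cut-offs for the p-value. It gives no z or p boundaries, and it does not exempt the primary endpoint from the general rule.

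**The concern.** A reader will normally take a significance level attached to an analysis as the level at which that analysis is tested. In a group-sequential design, though, the alpha spent at a look and the nominal cut-off at that look are different quantities after the first look. The test statistics are correlated, so part of the probability of crossing a later boundary has already been counted earlier. Three levels that add up to exactly the overall alpha suggest that the spent amounts were reported. 

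The success criterion for the primary endpoint is at stake. A final p-value between 0.0313 and 0.05 fails on one statement and passes on the other, and neither number is the final boundary that the named method yields. In an open-label trial that is still recruiting, the criterion should not be left to choose once the data are seen. The same figures will also guide the Data Monitoring Committee at the interim looks.

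**Working it through.** **Inputs from the article.** Overall alpha 0.05, one-sided (Sample size). O'Brien-Fleming method, with looks at 33%, 67% and 100% of the planned primary events (Statistical and analytical plans). Stated levels 0.0015, 0.0172 and 0.0313; general threshold 0.05.

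**Step 1: the sum.** 0.0015 + 0.0172 + 0.0313 = 0.0500.

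**Step 2: reproduce the stated figures.** Under the null, the three Z statistics are multivariate normal with correlation √(tᵢ/tⱼ) for tᵢ < tⱼ, where t = 1/3, 2/3, 1. The classical O'Brien-Fleming boundary is zₖ = C/√tₖ, with C chosen so that the total crossing probability is 0.05 one-sided. This gives C = 1.7096.

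| Look | z boundary | Nominal one-sided p | Alpha spent at the look | Stated |
|---|---|---|---|---|
| 1 | 2.961 | 0.0015 | 0.00153 | 0.0015 |
| 2 | 2.094 | 0.0181 | 0.01721 | 0.0172 |
| 3 | 1.710 | 0.0437 | 0.03126 | 0.0313 |

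The stated figures are the alpha-spent column. At looks 2 and 3 they differ from the nominal column.

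**Step 3: alternatives that do not give these figures.**
- Classical, two-sided 0.05: nominal 0.0005 / 0.0141 / 0.0451; increments 0.0005 / 0.0138 / 0.0357.
- Lan-DeMets O'Brien-Fleming-type spending, one-sided 0.05: increments 0.0007 / 0.0157 / 0.0336; nominal 0.0007 / 0.0161 / 0.0451.
- Looks at exactly 0.33 and 0.67, classical one-sided: increments 0.0015 / 0.0175 / 0.0311; nominal 0.0015 / 0.0184 / 0.0436. The stated figures therefore assume equal spacing.

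As corroboration, the increase from 450 to 462 patients is a factor of 462/450 = 1.027. The computed inflation for the one-sided design is 1.023, or 450 × 1.023 ≈ 460, which is close to the planned number.

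**Step 4: overall type I error under each reading** (same joint distribution, equally spaced looks).

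| Decision rule | One-sided | Two-sided p-values |
|---|---|---|
| Stated figures as p-value cut-offs | 0.0388 | 0.0399 |
| Interims at 0.0015 and 0.0172, final at p < 0.05 | 0.0552 | 0.0565 |
| Stated figures as alpha spent, cut-offs 0.0015 / 0.0181 / 0.0437 | 0.0500 | not applicable |

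**Step 5: power cost of using the stated figures as cut-offs (one-sided).** Write θ for the expected Z at full information.
- Effect with 90% power in a fixed design: θ = 1.645 + 1.282 = 2.926. Power is 89.4% with the nominal boundaries and 86.6% with the stated figures, a loss of about 3 points.
- The protocol's ratio of 0.46: the article gives no event count. Assume 462 patients, 20% lost, and 42% versus 22% recurrence. Events ≈ 462 × 0.8 / 2 × (0.42 + 0.22) = 118. Then θ = −ln(0.46) × √118 / 2 = 4.22. Power is 99.4% with the nominal boundaries and 99.2% with the stated figures, a loss of about 0.3 points.

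**Step 6: the final critical hazard ratio under the same assumption.** exp(−2z/√events) with 118 events gives 0.71 at level 0.0313 (z = 1.862), 0.73 at 0.0437 (z = 1.710) and 0.74 at 0.05 (z = 1.645). Without the 20% loss, events are 231 × 0.64 ≈ 148 and the values become 0.74, 0.76 and 0.76.

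**The case against.** The strongest reply is that false-positive control is intact on two of the three readings. Cut-offs that sum to 0.05 cannot give an overall error above 0.05 (the Bonferroni bound). The value of 0.0388 therefore meets the Sample size section's aim "to control the overall Type I error below 0.05". Read as alpha allocated per look, the figures spend exactly 0.05. A reader might infer that no version of the plan holds overall alpha at 0.05; the documents do not support that. This part of the reply stands. 

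A second reply is that the general 0.05 threshold closes a paragraph on many kinds of test, while the next paragraph gives the specific rule for the interim and final analyses, and the specific rule should govern. That is a reasonable reading. But the general rule follows directly on the log-rank and Cox analyses of sinus rhythm maintenance and contains no exception, so the other reading remains open. 

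A third reply is that the practical effect is small. At the protocol's own ratio the power loss is negligible, and the result changes only for a final p in a narrow band. This stands too and limits the severity. 

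Finally, boundaries at the actual event fractions are usually left to the analysis plan. That is true of recalculation, but here the article itself prints the levels and a conflicting threshold. The alpha-spent reading does not settle the matter either: the usable final boundary would still be unstated, and 0.05 would still conflict with it.

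**Conclusion.** The point holds as one of labelling and of an unresolved final threshold. The three figures are the per-look alpha increments of a classical one-sided 0.05 O'Brien-Fleming design with equally spaced looks, presented as the significance level of each analysis. The nominal cut-offs are about 0.0015, 0.0181 and 0.0437. 

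Used as cut-offs, the stated figures are conservative (0.039 rather than 0.05). They cost about 3 points of power at an effect with about 90% power, and about 0.3 points at a ratio of 0.46 with about 118 events. That event count is an assumption, not a figure from the article. Under this rule a valid positive result is lost only if the final one-sided p lies between 0.0313 and 0.0437. 

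Type I error is inflated only if the general 0.05 rule is applied at the final look after the stated interims: about 0.055 one-sided or 0.056 two-sided. It would go too far to conclude that the plan fails to control type I error however it is read. Severity: should be fixed.

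**What to change.** In the interim-analysis paragraph of Statistical and analytical plans, label 0.0015, 0.0172 and 0.0313 as alpha spent at each look. Beside them give the nominal p-value boundaries and their sidedness: 0.0015, 0.0181 and 0.0437 for the one-sided 0.05 design at equally spaced looks. If the test is to be two-sided at 0.05, the boundaries are 0.0005, 0.0141 and 0.0451, and the alpha-spent figures change to 0.0005, 0.0138 and 0.0357. State that the boundaries will be recomputed at the event fractions actually reached. 

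In the preceding paragraph, add to the general rule that the final-look boundary, not 0.05, decides the primary endpoint. 

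The cost is a wording amendment and a short boundary calculation. No patients or visits are added. It should be done before the first interim look or, if that has passed, before any further look at the data by treatment group.
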